### **Investigations at visit 7 (End of trial)**

After a 52-week treatment phase, the last visit 7 will be performed. The end of trial visit may be conducted any time during regular business hours and marks the trial completion that must be recorded in the eCRF.

- V7 will be scheduled  $12 \pm 2$  weeks after V6
- Physical examination
- Vital signs
- Height and weight
- Previous and concomitant diseases
- Previous and concomitant treatments
- Spirometry/Oscillometry  $\geq 4$  years pre-dosing
- Laboratory
- Download/review TIPP diary App
- Check study medication compliance
- Collect study medication/drug accountability
- Assessment of asthma control according to GINA guidelines
- TRACK test
- Complete CGI-C at end of treatment
- AEs
- Concomitant therapy

Please refer to the flow chart (trial schedule and section 3, Figure 2) for the examinations and procedures to be performed in case of early termination of patients who have received at least one dose of study medication.

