### **Pulmonary Function Testing**

#### **a) Spirometry**

PFTs will only be performed in  $\geq 4$ -year-olds who are capable of providing PFTs of acceptable quality. Repeatability criteria for preschoolers should be used: The patient should produce at least two acceptable curves, where the second-highest FVC and FEV1 are within 0.1 L or 10% of the highest value, whichever is greater (56). In a recent own investigation we found the following: According to the new American Thoracic Society/European Respiratory Society (ATS/ERS) guidelines, 74.6% of the children aged 4–6 years could perform at least 2, repeatable measurements in the healthy status (57, 58).

PFTs will be recorded whilst the patient is in a sitting position at the time points specified in the study flow chart. Spirometry will be performed according to the ERS. All lung function tests will

be repeated until three technically acceptable measurements have been made and the best of these three measures will be recorded in the CRF. The following variables will be documented: VC [L, % pred], FEV1 [L, % pred], FVC [L, % pred], FEV1/FVC (Tiffenau-Index).

Calibration of spirometry equipment is mandatory on all visit days and calibration logs should be stored as source data. The spirometers and their use, including daily calibration, must meet ATS/ERS criteria (57). If necessary, the sponsor may provide a SOP to the centers.

b) Impulse oscillometry

Impulse oscillometry (IOS) is a breathing analysis at rest that requires little cooperation. Thus, it can be performed in relatively young children. IOS parameters can differentiate between central and peripheral airways. There is evidence that asthma exacerbations in infancy are related to an inflammation of the small airways. In an own study, we included 75 children aged 4–7 years with mild asthma in the infection-free interval in the summer (58). The results showed that the IOS predicted significantly mild asthma exacerbations in autumn and winter (AUC: Rrs5 78%, Xrs5 70%, and Rrs5-20 77%). This was not the case for spirometry (FEV1) and methacholine provocation (both AUC 61%).

c) IOS measurement

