### Additional secondary endpoints for children aged 4 years and older:

Only applicable for patients able to perform technically acceptable (and reproducible) pulmonary function tests.

- The forced expiratory volume in one second (FEV1) and the forced vital capacity (FVC) measured 30 minutes post IMP will be compared to pre-dosing FEV1 and FVC values at visit 2.
- Trough FEV1 and through FVC response will be determined at visit 3, visit 4, visit 5 and visit 7. Trough FEV1 is defined as the FEV1 and FVC measured approximately 24 hours after the last IMP inhalation. Response is defined as a 10% improvement in FEV1 or FVC, respectively, compared to baseline (visit 2, pre-dosing).
- Potential biomarkers for treatment response (Eosinophils, IgE, specific IgE to common allergens: birch, grass, *Dermatophagoides pteronyssinus*, *Alternaria*, *Cladosporium*, cat,

dog, hen's egg, cow's milk and peanut)

**Assessment of safety:** Safety will be ensured by analysis of symptom scores and rescue medication by electronic diary, and AEs.

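### The 10% FEV1/FVC responder rule names no scale and no growth correction, so read in litres its week-52 rate would largely reflect a year of growth

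*Protocol*

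**What the plan says.** Sections 3.4, 6.1 and 8.3 of the protocol each list additional secondary endpoints for children aged 4 years and older who can perform acceptable lung function tests. Trough FEV1 and FVC response "will be determined at visit 3, visit 4, visit 5 and visit 7", and the rule is: "Response is defined as a 10% improvement in FEV1 or FVC, respectively, compared to baseline (visit 2, pre-dosing". None of the three sections names a unit or a correction for body size.

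V7 comes a year after V2: "After a 52-week treatment phase, the last visit 7 will be performed". All children are under 6 at V1.

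Section 6.2 (spirometry) accepts two curves "where the second-highest FVC and FEV1 are within 0.1 L or 10% of the highest value, whichever is greater". It then states that "the best of these three measures will be recorded in the CRF", and lists the recorded scales as "VC [L, % pred], FEV1 [L, % pred], FVC [L, % pred". The trial schedule has height measured at every clinic visit.

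Section 8.3.2 sends categorical secondary endpoints to a chi-square or Fisher's exact test and continuous ones to a t-test or Mann-Whitney U test. The protocol gives no growth rate, no between-visit variability and no expected responder rate.

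**The concern.** FEV1 and FVC are volumes, and children of 4 to 5 grow over the 52 weeks between baseline and V7. If the rule is applied to litres, a child whose asthma has not changed can cross the 10% line by growing. The same rule would then mean different things at week 6 and at week 52.

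The threshold is also low against measurement noise, since it does not exceed the disagreement the protocol tolerates within one session.

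Because both litres and % predicted are recorded, two analysts could follow the text faithfully and report very different responder rates. What is at stake is the meaning of the lung-function result and the power to detect an effect in a small subgroup.

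**Working it through.** The protocol has no figure of its own to reproduce on this point. Its only calculated figure, the 152 patients in section 8.1, comes from the log-rank calculation for the primary endpoint and uses no lung-function input.

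**1. Growth (assumed).** Take height 100–115 cm, gain 5–8 cm per year, and volume proportional to height to the power k = 2 to 3. Annual growth is g = ((h + d)/h)^k − 1.
- Lowest: (120/115)² − 1 = 8.9%.
- Highest: (108/100)³ − 1 = 26%.
- Most combinations exceed 10%.

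**2. Chance of meeting the rule with no drug effect.** FEV1 and FVC are treated separately. For week w and between-visit coefficient of variation CV (assumed):

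P = 1 − Φ([ln 1.10 − (w/52)·ln(1 + g)] / (√2·CV))

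Example: g = 12%, CV = 5%, w = 52 gives (0.0953 − 0.1133)/0.0707 = −0.255, so P = 60%.

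| Annual growth | V3, week 6 | V4, week 16 | V5, week 28 | V7, week 52 |
|---|---|---|---|---|
| 0% | 9 / 17% | 9 / 17% | 9 / 17% | 9 / 17% |
| 9% | 11 / 19% | 17 / 24% | 24 / 31% | 45 / 46% |
| 12% | 12 / 20% | 20 / 27% | 31 / 36% | 60 / 57% |
| 15% | 13 / 21% | 23 / 30% | 39 / 42% | 74 / 67% |

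Each cell gives CV 5% / CV 7%. At 20% growth the V7 figures are 89 / 81%. Over a wider CV range of 3.6–10%, the zero-growth rate is 3–25%.

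**3. Threshold against the acceptance limit.** The limit is the greater of 0.1 L and 10%. As a share of the volume, 0.1 L is 14% at 0.7 L, 12.5% at 0.8 L and 10% at 1.0 L. The 10% cut-off therefore equals the limit at 1.0 L and above, and is below it for smaller volumes.

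**4. Contrast between arms.** Assume a true 5% drug gain and CV 5%. V7 response, placebo against tiotropium:
- no growth: 9% vs 26% (17 points, odds ratio 3.5)
- 12% growth: 60% vs 83% (23 points, odds ratio 3.2)
- 15% growth: 74% vs 91% (17 points)
- 20% growth: 89% vs 97% (8 points)

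**5. Power.** If ages are evenly spread over 1–5 years (assumed) and 74.6% of the older children perform acceptably (the sponsor's earlier series cited in section 6.2), then 152 × 2/5 × 0.746 ≈ 45 children contribute, about 22 per arm before dropout. With the same 5% gain, two-sided 5%, and growth from 0 to 20%:

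| Analysis | CV 5% | CV 7% |
|---|---|---|
| Fisher's exact test on the 10% rule, litres | 5–31% | 9–16% |
| Uncorrected chi-square on the 10% rule, litres | 13–42% | 17–25% |
| t-test on continuous size-corrected change | 61% | 36% |

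The standardised difference for the t-test is ln 1.05/(√2·CV), which is 0.69 at CV 5% and 0.49 at CV 7%. At zero growth Fisher's test has 21% and 14%, so much of the loss comes from dichotomising alone.

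**The case against.** A reader might infer that most untreated children would count as responders by week 52. The documents do not support that. It needs the litres reading, which is nowhere stated, and growth above 10% per year, which is plausible but not in the protocol; at 9% growth the V7 figure is 45–46%. On % predicted, which the protocol also records, growth is largely removed. Controls are not untreated either: section 1.5 gives them placebo on top of at least ICS. The effect is also mainly late: up to 15% growth, no visit before V7 reaches a majority.

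A reader might also equate the 10% threshold with the measurement error. Section 6.2 sets a within-session acceptance limit between the two best curves, and the best value is recorded. That is not between-visit error. If 10% were a 95% limit for the difference between two visits, the CV would be 0.10/(1.96·√2) = 3.6% and only about 3% would respond by chance without growth.

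Nor does growth create a false difference. It raises both randomised arms, and on the assumptions above the absolute contrast widens at moderate growth and narrows only when growth is high.

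Finally, scale and model could be left to the SAP, which is not shown. That holds for the model. It holds less well for the definition, because the protocol itself fixes the endpoint and the cut-off and leaves the unit open. All the other objections stand and limit the size of the point; none supplies the missing scale.

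**Conclusion.** The point holds in limited form. The rule is incomplete as written: it has no scale, no size correction, and a cut-off that does not exceed the protocol's own within-session limit. At 12% growth and CV 5%, the choice between litres and a growth-free scale moves the V7 placebo rate from about 60% to about 9%. The rate cannot be taken as a treatment response, nor compared between V3 and V7, unless the scale is fixed. Growth, height scaling, CV, drug gain and subgroup size are all assumptions, so the figures show the likely order of magnitude only.

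Severity is minor. This is a secondary endpoint in a subgroup, the randomised comparison stays unbiased, and neither the primary analysis nor the sample size is touched.

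**What to change.** In sections 3.4, 6.1 and 8.3, make the lung-function endpoint the change from V2 pre-dose in % predicted FEV1 and FVC at V3, V4, V5 and V7, analysed as a continuous variable with the baseline value as covariate. Name one reference equation for all sites. If a responder rate is kept as a supporting summary, define it on % predicted, write at least 10%, and say whether that is relative or in percentage points.

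The cost is wording only: % predicted and height are already collected. Section 8 allows the SAP to modify the planned analyses, so the SAP should carry the same text, settled before unblinding. There are two downsides: the responder rate is no longer the main lung-function result, and % predicted depends on the reference equation chosen.

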### 8.3.1 Definition and analysis of primary endpoint

The primary analysis is the comparison of time to first severe exacerbation within 12 months of therapy between groups. This means especially that observations after 12 months will be censored. Dropouts because of lack of efficacy will be considered as an exacerbation. All other dropouts will be censored. The comparison will be done on a two-sided significance level of  $\alpha = 5\%$ .

The primary hypotheses are:

$$H_0: h_E/h_C = 1 \quad \text{versus} \quad H_1: h_E/h_C \neq 1$$

Where  $h_E$ ,  $h_C$  are the hazards in the experimental treatment group and the control treatment group respectively.

The time to first severe exacerbation will be analyzed by Cox regression with factor treatment group and the covariates age group and center assuming a constant hazard ratio over time. The constant hazard ratio assumption will be checked by Schoenfeld residuals. The primary analyses will be performed in the ITT population. Treatment differences will be displayed by estimates of the hazard ratios and 95% confidence intervals.

Several sensitivity analyses will be performed. The primary analysis Tiotropium + at least ICS versus placebo + ICS will be repeated additionally adjusted for LABA and LTRA use. This analysis is not primary since LABA use is not treatment independent. Additional covariates might be considered in the Cox model as well as the assessment of the per-protocol effect (both specified in the SAP). A time to recurrent event analysis is also performed. Since a substantial correlation between the events is expected a Prentice Williams and Peterson (PWP) model with the age group and center will be employed. Additionally, a Kaplan-Meier analysis including a Kaplan-Meier plot will be done.

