### 3.2 Number of patients and trial centers

It is planned to include 152 patients (randomized) in the clinical trial, currently 13 trial sites agreed to participate.

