### 3.3 Selection of trial population

A sufficient number of asthmatic patients aged 1–5 years of either sex will be enrolled in the study to ensure that 152 children are entered (randomized) in the trial. Recruitment is competitive. Additional sites may be initiated and 'non-productive' sites may be closed to ensure the trial timelines.

Participation in the oscillometry measurements is optional and not a prerequisite for patients to participate in the trial. The number of patients participating in the oscillometry measurements is not limited.

Every effort should be made to keep patients in the study until completion of all study procedures. Patients who discontinue after randomization may not be re-enrolled later. A record will be kept of all patients who fail to complete all study visits and their reasons for early discontinuation.

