### 3.5 Measures taken to minimize/avoid bias

#### 3.5.1 Randomization

A randomization list will be generated by an independent person from IZKS using a SAS® based computer program with permuted blocks without stratification factors. The randomization list assigns an identification code (medication number) to a treatment. The randomization list will be kept in safe and confidential custody at IZKS Mainz. Randomization number will be documented in the eCRF system with an identification code to a patient without knowing the treatment behind the medication number.

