| Not at all
 20                                                                                                                                                                                                                                          | Once or twice
 15 | Once every week
 10 | 2 or 3 times a week
 5 | 4 or more times a week
 0 |
| 5. During the past 12 months , how often did your child need to take oral corticosteroids (prednisone, prednisolone, Orapred®, Prelone®, or Decadron®) for breathing problems not controlled by other medications?                                                          |                                              |                                                |                                                   |                                                      |
| Never
 20                                                                                                                                                                                                                                               | Once
 15          | Twice
 10           | 3 times
 5             | 4 or more times
 0        |

**Figure 4:** Test for respiratory and asthma control in kids (TRACK).

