### 8.1 Sample size

Sample size calculations were based on results published by Vrijlandt E et al. (33). In this study, children aged 1–5 were treated with Tiotropium 5 µg vs placebo as add-on to ICS. After 105 days, 29% of the Tiotropium 5µg group had an asthma exacerbation with pneumonia or asthma worsening, whereas 55.9% of the placebo group had an event. For the present study, it can be assumed that most patients treated with ICS + placebo will suffer from one severe exacerbation within one year, therefore a rate of 90% of placebo patients with a severe exacerbation after one year is anticipated. For the Tiotropium group, a rate of 75% is assumed. The estimation of the difference in rates between the placebo and the Tiotropium group is performed conservatively, assuming a smaller difference than observed after 105 days in the study of Vrijlandt E et al (33). The assumed dropout rate of 15% is converted into a group-loss hazard (0.16) and considered in the sample size calculation. With an event rate of 90% in the control group and 75% in the Tiotropium group and a drop-out-rate of 15%, the sample size will amount to 152 patients when applying a two-sided log-rank test with a hazard ratio of 0.60, a significance level of  $\alpha = 0.05$  and a power of 0.8. The power calculation was performed with PROC POWER in SAS® 9.4.

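### Entering centre site by site in the primary Cox model (13 or more sites, 152 children) lifts the nominal 5% test to about 7%

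*Protocol*

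**What the plan says.** Section 8.3.1 sets out the primary analysis in one sentence: "The time to first severe exacerbation will be analyzed by Cox regression with factor treatment group and the covariates age group and center", with a constant hazard ratio assumed. On the level it says "The comparison will be done on a two-sided significance level of" 5%. The population is ITT. The synopsis gives the same model, and the recurrent-event (PWP) sensitivity analysis in 8.3.1 also includes age group and centre.

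Three other sections bear on the centre term:
- Section 3.2 plans 152 randomised children and says "currently 13 trial sites agreed to participate".
- Section 3.3 says "Recruitment is competitive" and allows sites to be opened or closed during the trial.
- Section 3.5.1 randomises "with permuted blocks without stratification factors", so centre is not part of the allocation scheme.

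The sample size in 8.1 rests on a different test, one without covariates: "the sample size will amount to 152 patients when applying a two-sided log-rank test with a hazard ratio of 0.60". The protocol does not say how centre is coded or whether small centres are combined.

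**The concern.** The plain reading of centre as a covariate is one indicator per site. With 13 sites that is 12 parameters, plus age group and treatment, for roughly 120 events and fewer than 12 children per site on average. Competitive recruitment will probably leave some sites much smaller than that.

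A Cox model with this many nuisance parameters for its events overfits. The log hazard ratio is pushed away from zero, and the model-based standard error does not reflect the extra variability. A significance test and a 95% interval built on that standard error are both too optimistic. This is the trial's primary test, so the stated 5% level, the interval and the size of any benefit are all affected.

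**Working it through.** **Inputs from the protocol.** N = 152, two-sided 5%, power 0.80, HR 0.60, one-year event rates of 90% and 75%, group-loss hazard 0.16 (8.1); censoring at 12 months and the model terms (8.3.1); 13 sites (3.2); unstratified permuted blocks (3.5.1).

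**The plan's own figure.** Schoenfeld events: 4 × (1.960 + 0.842)² / (ln 0.60)² = 120.3, so 121. The control hazard is −ln 0.10 = 2.303 and the tiotropium hazard is 0.60 × 2.303 = 1.382. With loss hazard 0.16, the chance of an observed event in one year is λ/(λ + 0.16) × [1 − exp(−(λ + 0.16))]:
- control: 0.855
- tiotropium: 0.704
- mean: 0.780

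Then 121 / 0.780 = 155, within 3% of the stated 152. At N = 152 the expected events are 152 × 0.780 = 118.5, with power 79.4%. The figure is reproduced. It is a figure for a log-rank test and makes no allowance for centre terms.

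**Parameters.** 13 − 1 = 12 centre indicators; 152 / 13 = 11.7 children per centre.

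**Rejection under HR = 1.** There were 12,000 simulated trials per scenario (Monte Carlo error about 0.2 points). Assumed, because the protocol does not give them: 1:1 blocks of 4, two age groups, exponential times, and the centre sizes and effects shown. Except in the first row, centre effects have SD 0.3 on the log hazard and the age hazard ratio is 1.3. Entries are Wald rejection rates.

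| Scenario | Mean events | Centre indicators | Age group only | Strata by centre, unpooled |
|---|---|---|---|---|
| 13 equal centres, no centre or age effect, 90% event rate | 130 | 6.6% | 5.0% | 5.1% |
| 13 equal centres, 90% | 132 | 7.2% | 5.5% | 5.2% |
| 13 unequal centres, 82.5% | 122 | 6.7% | 5.4% | 5.1% |
| 13 equal centres, 60% | 92 | 7.0% | 5.5% | 5.6% |
| 18 equal centres, 90% | 132 | 7.6% | 5.0% | 5.0% |
| 600 children, 13 equal centres, 90% | 522 | 5.1% | 5.0% | 4.8% |

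Likelihood-ratio and score tests gave the same or slightly higher rates than the Wald test. A few fits in the unequal-centre row did not converge and were counted as non-rejections. The last row shows the cause: with enough children per centre parameter the excess disappears.

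**Standard error.** In the first scenario the mean model SE is 0.191 against a true SD of 0.205 (ratio 0.93, 7% too small). In the second it is 0.190 against 0.208 (ratio 0.91, 9% too small). This accounts for the size: the effective critical value is 1.96 × 0.93 = 1.83 or 1.96 × 0.91 = 1.79, with two-sided tail areas of about 6.8% and 7.3%.

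**Estimate at true HR 0.60.** With centre indicators the mean log hazard ratio corresponds to 0.571 in one set of simulations and 0.575 in another. The shift is ln 0.60 − ln 0.571 = −0.511 + 0.560 = 0.049, or 0.049 / 0.218 ≈ 0.2 of the true SD.

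**The remedy.** Strata with centres under 15 children pooled were simulated separately, with about 2,000 to 4,000 null trials per setting (Monte Carlo error about 0.3 to 0.5 points). Rejection was 4.9% to 5.7% and the mean HR was 0.598 to 0.603. Power at HR 0.60 was:
- pooled strata against age group only: 74.9% against 75.6%, 74.2% against 74.6%, and 74% against 75%, a cost of about 1 point or less
- unpooled strata against age group only: 71.1% against 76.2%, and 69–70% against 73–75%, a cost of about 4 to 5 points (another set gave 71.4% against 74.6%, about 3)

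The 78.3% power with unpooled indicators is reached at the inflated level and is not a fair comparison. These powers carry the assumed centre effects. They serve to compare models, not to revise the sample size.

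**The case against.** The strongest objection is that the protocol names centre but not its coding. A SAP, not available here, could pool small sites, and section 8 lets the SAP modify the plan. Keeping centre as a covariate but pooling sites under 15 children gave 5.5% to 5.9%, so most of the excess would go. This stands, and it makes the finding conditional. A reader might infer that the primary test runs at 7% whatever is done later. The documents do not support that. The point still belongs in the protocol, because 8.3.1 names the primary model's terms and section 8 requires major modifications of the primary analysis to appear in an amendment.

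The bias is also modest. The shift in the hazard ratio is about a fifth of a standard error, and rates near 8% in some smaller simulations with unequal centres are not borne out by the larger one (6.7%).

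A reader might further infer that omitting prior steroid courses is part of the error, since TRACK item 5 asks at visit 1 "how often did your child need to take oral corticosteroids" over the past 12 months. That does not follow. Leaving out a prognostic covariate does not inflate the type I error. Section 8.3.1 leaves room for further covariates among the sensitivity analyses, and TRACK itself is a secondary endpoint. The item counts oral courses only, capped at four or more, and so misses the rectal prednisolone and hospitalisation that also define the endpoint. Any power gain would rest on an assumed hazard ratio per course that the protocol does not supply.

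**Conclusion.** The concern holds, on condition that centre enters as one unpooled indicator per site. The nominal 5% test then rejects 6.6% to 7.2% of true nulls with 13 sites, that is 6.6/5 = 1.32 to 7.2/5 = 1.44 times the stated rate, and 7.6% with 18 sites. The 95% interval is correspondingly too narrow and the benefit slightly overstated.

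The excess appeared with equal and unequal centres, with and without centre effects, at event rates from 60% to 90%, and with all three tests. The exact figures rest on assumed centre sizes, centre and age effects, block size and number of age groups. The PWP model carries the same covariates but was not simulated.

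**What to change.** In 8.3.1 and the synopsis, replace centre as a covariate by a Cox model stratified by centre, with treatment and age group as covariates. Pool small centres, for example those with fewer than 15 randomised children, into one stratum by a rule fixed on blinded data before unblinding. Make the same change in the PWP model.

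State what the rule does. The mean centre size of 11.7 is below 15. In simulation about 73% of children fell into the pooled stratum with equal centres and 41% with unequal ones, leaving on average 3.5 and 4.8 strata. When centres are similar in size, the analysis therefore comes close to adjusting for age group only, which also kept near its level (5.0% to 5.5%). That is why pooling costs only about 1 point of power, while full stratification costs about 4 to 5. The cut-off is a choice and should be justified.

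The cost is one sentence in each place, handled as an amendment, with no new data. Adding the TRACK item 5 count as a covariate is an optional suggestion. Its gain cannot be quantified from the protocol, and it is not needed to correct this point.
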